### Primary outcome

2.13

#### Pain

2.13.1

The primary outcome is average pain in the midfoot whilst walking in the last 7 days scored using an 11‐point NRS with terminal descriptors of 0 (‘no pain’) and 10 (‘worst pain imaginable’). This outcome measure has been used as a primary outcome measure in a feasibility trial that investigated arch contouring foot orthoses for midfoot OA [35] and has been recommended for clinical trials in OA [40]. Although there are no studies that have assessed the responsiveness of the NRS specifically in midfoot OA, the NRS has been shown to be more responsive, easier to administer and preferred by adults compared to other pain scales [41]. In people with chronic musculoskeletal pain, the minimal clinically important difference of the NRS has been reported to be between 1 and 2 points [42, 43].

### Secondary outcomes

2.14

#### Function

2.14.1

Function will be assessed using the walking/standing subscale of the Manchester–Oxford Foot Questionnaire (MOxFQ) [44]. The MOxFQ has been shown to be valid (content and construct), have high retest reliability (intra‐class correlation coefficient 0.96) [45] and have a high degree of internal consistency (Cronbach *α* 0.92) for the walking/standing subscale [46].

#### Participants' perception of overall treatment effect

2.14.2

Participants' perception of overall treatment effect will be measured using the self‐reported global rating of change (GROC) scale [47] at 12 weeks. Participants will be asked: ‘With respect to your midfoot osteoarthritis, how would you describe yourself now compared to the start of the study?’, with the response measured using a 15‐point Likert scale (ranging from ‘a very great deal worse’ to ‘a very great deal better’). This outcome will then be dichotomised into the categories of ‘effective’ (‘a very great deal better’, ‘a great deal better’, ‘a good deal better’ and ‘moderately better’) and ‘ineffective’ (‘somewhat better’, ‘a little better’, ‘about the same, hardly any better at all’, ‘no change’, ‘about the same, hardly any worse at all’, ‘a little worse’, ‘somewhat worse’, ‘moderately worse’, ‘a good deal worse’, ‘a great deal worse’ and ‘a very great deal worse’) [48].

#### Physical activity

2.14.3

Levels of physical activity will be measured using the Incidental and Planned Exercise Questionnaire (IPEQ) [49]. The IPEQ is a valid and reliable 12‐item questionnaire assessing low, basic and high‐intensity physical activities with a week recall [49].

#### Health‐related quality of life

2.14.4

Health‐related quality of life will be measured using the Short Form‐12® Version 2.0 (SF‐12v2®) [50], a 12‐item questionnaire that is a reliable and valid measure of physical and mental health [50].

### Use of co‐interventions

2.15

Participants will be asked to document the use of any co‐interventions at 4, 8 and 12 weeks via online questionnaires. They will be asked if they have received or used any new treatment to relieve the pain that they are experiencing in the midfoot. This includes, but is not limited to, the use of any taping or bracing, visits to healthcare providers, use of any creams/rubs or use of any medication such as anti‐inflammatory drugs. It also includes the use of topical NSAIDs and footwear changes recommended as part of the clinical guideline‐based information and support. Participants will be asked to document the type of treatment, the date(s) they received or used the treatment and if relevant, the dosage and frequency of the treatment used. Participants will also be asked if they have changed the footwear they normally wear. To minimise participant burden, the use of co‐interventions will be documented on the day with recall over the previous 4 weeks rather than daily entry surveys [51, 52, 53].

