## INTRODUCTION

1

Midfoot osteoarthritis (OA) is a common and painful condition that affects 1 in 8 adults over the age of 50 [1]. The midfoot is made up of several articulations including the tarsometatarsal joints (first, second and third cuneo‐metatarsal joints [CMJs] and fourth and fifth cuboid‐metatarsal joints), the navicular‐first, ‐second and ‐third cuneiform joints (N1CJ, N2CJ and N3CJ), the talonavicular joint (TNJ) and the calcaneocuboid joint [2, 3, 4, 5, 6]. Although midfoot OA is often described as dorsal midfoot pain aggravated by weight‐bearing activities [7], there is no universally agreed definition or diagnostic criteria for this condition [4, 8, 9]. Midfoot OA typically affects more than one joint, and three phenotypes have been reported based on the pattern of joint involvement observed in radiographs: the medial midfoot (TNJ, N1CJ or first CMJ), the central midfoot (second CMJ) or both the medial and central midfoot joints [4]. Midfoot OA is the most disabling type of foot OA [3] and significantly impacts both physical and mental health‐related quality of life [10, 11]. People with midfoot OA experience physical impairments, including reduced foot and leg muscle strength [12], and have limitations in activities, such as walking and climbing stairs [13, 14], with over 80% reporting the condition to be disabling [14]. In addition, they report increased levels of anxiety and depression [13, 14]. The aetiology of midfoot OA is multi‐factorial and not completely understood. However, several factors are associated with the condition including older age, female sex, manual occupations, obesity, pain in other weight‐bearing joints, previous foot and ankle injury, and having other non‐musculoskeletal comorbidities [14].

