### Participants

2.3

One hundred and forty participants will be recruited. To be eligible for inclusion, participants must: (i) be aged ≥18 years, (ii) have pain in the midfoot joints (located in at least one area in a predetermined dorsal midfoot region [26]) for at least 3 months that is aggravated by weight‐bearing activities, (iii) have pain in the midfoot when walking during the last 7 days that is rated an average of at least 3 out of 10 in severity on an 11‐point numerical rating scale (NRS) (where 0 represents ‘no pain’ and 10 represents the ‘worst pain imaginable’), (iv) have radiographic evidence of midfoot OA (defined in this trial as a minimum score of 1 for either observations of joint space narrowing or osteophytes in at least one of the midfoot joints in either radiographic view) assessed using the La Trobe University Atlas of Foot OA [27], (v) be able to walk household distances (more than 50 m) without the aid of a walker, crutches or cane, (vi) be willing to regularly wear shoes that will accommodate shoe inserts, and (vii) be willing to attempt to not use co‐interventions (including pain relieving oral medications) during the study period.

Participants will not be eligible for inclusion if they: (i) have had previous ipsilateral foot surgery or are planning surgery in the next 12 weeks, (ii) have OA secondary to other issues such as major trauma, (iii) have the presence of other foot or ankle condition(s) or have pain in another location that is greater than the pain in the midfoot, (iv) have any musculoskeletal or systemic medical conditions (e.g. suspected inflammatory joint disease or neurological conditions) that could make them unsuitable for inclusion or confound pain and functional assessments of the midfoot, (v) are unable to speak and read English, (vi) have had treatment that includes the use of any foot orthoses (including shock absorption shoe inserts), ankle braces and/or, received intra‐articular injections at the midfoot in the previous 12 weeks, and (vii) have dementia or any cognitive impairment.

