#### Clinical guideline‐based information and support

2.10.3

Participants in both groups will receive a standardised education package derived from clinical guidelines for management of OA [37, 38] and our recent survey on the current practices of Australian podiatrists for the management of midfoot OA (manuscript in preparation). Education will include guidance regarding midfoot OA (i.e. information on epidemiology, location of affected joints and associated factors), OA flares, advice relating to exercise such as activity modification, weight loss, the use of topical non‐steroidal anti‐inflammatory drugs (NSAIDs) and footwear.

Participants in both groups will be advised to use their allocated shoe inserts in their footwear for as much time as they can during the day for the 12 weeks of the trial. Insole wear will be monitored by recording the average days per week, plus the average number of hours per day the participant has worn the arch contouring foot orthoses or sham inserts, assessed via online questionnaires at each 4‐weekly timepoint. Participants will be requested to attempt to not use co‐interventions (including pain relieving oral medications) during the study, but if they do, they are required to document the use of co‐interventions in the 4‐weekly online questionnaires.

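### As described, the 4-weekly co-intervention question asks only about treatment for midfoot pain, which is narrower than the request to avoid and document oral pain relief

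*Protocol article*

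**What the plan says.** Section 2.3 (Participants) requires willingness to try to go without co-interventions, and names oral pain relief as one of them. Section 2.10.3 repeats the request and adds a duty to record use: "including pain relieving oral medications) during the study, but if they do, they are required to document the use of" co-interventions in the 4-weekly questionnaires. Neither section limits this by the site of pain or the reason for taking the medicine.

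Section 2.15 (Use of co-interventions) opens broadly: "Participants will be asked to document the use of any co‐interventions at 4, 8 and 12 weeks via online questionnaires". It then describes the question put to participants, which is about new treatment "to relieve the pain that they are experiencing in the midfoot". An open-ended list of examples follows, among them "use of any medication such as anti‐inflammatory drugs". The only further item described without reference to midfoot pain is a change in usual footwear.

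The abstract lists use of co-interventions as a secondary outcome. Section 2.20 compares its frequency between arms by relative risk, risk difference and number needed to treat.

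**The concern.** Oral pain relief acts on the whole body. A tablet taken for a painful knee or hip can also lower the primary outcome, average midfoot pain on walking over the last 7 days. The protocol seems to accept this, since it names oral pain relief as something to avoid without mentioning a site. Yet a participant who answers the described question literally would leave that tablet out.

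At stake is the reading of the trial. If such use differed between arms, the co-intervention comparison could not show it. A reader could not judge how much of the 12-week pain difference to ascribe to the device. The gap is one of body site, so deleting the word *new* from the question would not close it: a tablet newly started for hip pain is missed either way.

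**Working it through.** **1. The passages side by side**

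| Place | What it covers | Limited to midfoot pain? |
|---|---|---|
| 2.3, inclusion (vii) | Try not to use co-interventions, including oral pain relief | No limit stated |
| 2.10.3 | Same request, plus a duty to document use every 4 weeks | No limit stated |
| 2.15, opening sentence | Any co-interventions | No limit stated |
| 2.15, question as described | New treatment | Yes |
| 2.15, list of examples | Types of treatment, open-ended | Yes, as examples under that question |

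The open-ended list widens the types of treatment covered. It does not widen the reason for taking them.

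**2. Does another record fill the gap?**

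- Section 2.5 records medications at enrolment only, so it shows prior use and not use during the trial.
- Section 2.17 records the type, body location, frequency and/or severity of adverse events. It does not record medicines taken.

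**3. Can such participants enrol?** Exclusion (iii) in 2.3 removes people with other foot or ankle conditions, and those who "have pain in another location that is greater than the pain in the midfoot". Exclusion (iv) removes people with musculoskeletal or systemic conditions that could make them unsuitable or confound assessment of the midfoot. Together these narrow the group. Lesser pain at another site does not by itself exclude, and the Introduction names pain in other weight-bearing joints among the factors associated with midfoot OA.

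**4. The plan's own figure.** Inputs from 2.19: difference 1.1, SD 2.2, alpha 0.05 (taken as two-sided), power 80%, 10% loss. The normal approximation gives 63 per arm, and 2 × 63 / 0.90 = 140. The stated 140 is reproduced, and this point does not affect it.

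**5. Illustrative size.** The documents give neither a rate of such use nor its effect on midfoot pain, so both are assumptions.

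Shift = (difference between arms in the proportion using) × (points of pain lowered in users)

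| Imbalance | Effect in users | Shift | Share of 1.1 |
|---|---|---|---|
| 0 | any | 0 | 0% |
| 10 points | 1 | 0.10 × 1 = 0.1 | 9% |
| 10 points | 2 | 0.10 × 2 = 0.2 | 18% |
| 20 points | 1 | 0.20 × 1 = 0.2 | 18% |
| 20 points | 2 | 0.20 × 2 = 0.4 | 36% |

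More use in the sham arm shrinks a true benefit; more use in the orthosis arm enlarges it. A true 1.1 would thus appear as anything from 1.1 − 0.4 = 0.7 to 1.1 + 0.4 = 1.5. In the shrinking direction, the power of a t-test with 63 per arm is 79.5% at 1.1, about 72% at 1.0 and about 43% at 0.7.

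**The case against.** The strongest reply is that a journal article condenses the questionnaire. The form itself is not shown, 2.15 opens with any co-interventions, and 2.10.3 tells participants to document oral pain relief. Some will report it unprompted. This stands in part: a reader might infer that such use goes unrecorded, but the document shows only that it is not asked for, as the question is described. It does not dispose of the point, because the article states the scope of the question, and that scope is narrower than the request it is meant to monitor.

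It can also be said that *co-intervention* simply means other treatment for midfoot OA, so that the sections agree. That reading is possible. It would still leave systemic pain relief for other sites outside the comparison.

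A reader might further infer that anyone with lesser pain elsewhere is admitted. Exclusion (iv) prevents that reading, since it can remove people whose other conditions would confound midfoot assessment. The Introduction, for its part, describes midfoot OA in general and not this screened sample.

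Finally, a reader might infer that the primary result is biased. The documents do not support this. Arms are randomised and participants blinded by limited disclosure, so balanced use is a natural reference case. An imbalance would have to be present in the 7 days that the 12-week score covers. If the device itself provoked pain elsewhere, the adverse event record would give some sign of it, though not of the tablet taken. The ANCOVA includes only baseline score and group, so better recording would not alter its estimate.

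**Conclusion.** The mismatch between 2.15 and sections 2.3 and 2.10.3 is real and should be corrected. Followed as written, the co-intervention comparison may undercount systemic pain relief and could not reveal an imbalance in use for other sites. The harm is to that secondary outcome and to the interpretation of the primary result; the sample size and the primary analysis stand.

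The size cannot be established from the document. It may be zero. The range of 0 to 0.4 points, in either direction, rests wholly on the assumed imbalance of 0 to 20 percentage points and the assumed 1 to 2 point effect in users.

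**What to change.** Reconcile 2.3, 2.10.3 and 2.15, stating whether the request to avoid oral pain relief extends to other sites; that decision is for the trial team. Whatever they intend, the recording should be broad: at 4, 8 and 12 weeks, ask about any pain-relieving or anti-inflammatory medicine used for any reason in the last 4 weeks, with body site or reason as a follow-up field. Report any-site oral use by arm beside midfoot-specific use.

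Recruitment began in September 2023 and 2.20's comparisons await follow-up expected to end by December 2024 (3.1), so some or all participants may have answered the present question. Report their co-intervention data separately and state the limitation. The enrolment medication list can describe prior use only.

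The cost is one reworded item, one extra field, slight participant burden, one more row in the co-intervention table, and data that are not fully comparable before and after the change.

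### The trial asks participants to try to avoid co-interventions, yet advises topical NSAIDs and footwear and counts them as co-interventions, which blurs that secondary comparison

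*Protocol article*

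**What the plan says.** The protocol makes four statements that bear on each other.

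- **Eligibility (section 2.3).** Participants must "be willing to attempt to not use co‐interventions (including pain relieving oral medications) during the study period".
- **Instruction during the trial (section 2.10.3).** The same thing is asked of both arms: "Participants will be requested to attempt to not use co‐interventions (including pain relieving oral medications) during the study". Any use must be reported in the four-weekly questionnaires.
- **Education (section 2.10.3).** "Participants in both groups will receive a standardised education package derived from clinical guidelines for management of OA". The listed topics include "weight loss, the use of topical non‐steroidal anti‐inflammatory drugs (NSAIDs) and footwear".
- **Definition (section 2.15).** Co-interventions are new treatments for the midfoot pain, with taping or bracing, provider visits, creams and medication as examples. The section then adds: "It also includes the use of topical NSAIDs and footwear changes recommended as part of the" information and support given by the trial.

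The Abstract lists co-intervention use among the secondary outcomes. Section 2.20 gives its frequency as an example of a dichotomous outcome, to be compared by risk ratio, absolute risk difference and NNT. Section 2.15 has participants record the kind of treatment, when it was used and, where relevant, how much and how often. It also asks separately whether usual footwear has changed.

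**The concern.** The same act is advised in one place, discouraged in another, and then scored as a departure. Nothing in the protocol exempts the package's own recommendations from the request, and nothing in the stated analysis separates them from treatment that participants sought for themselves.

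What is at stake is the meaning of a secondary outcome. A between-arm comparison of co-intervention use is most useful for judging whether one arm sought more additional pain treatment than the other. The protocol does not state that purpose; it is the usual reason for making the comparison. If many people in both arms count as users because they did what the trial advised, the comparison moves towards no difference, and its NNT treats following trial advice as the same event as seeking other care.

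**Working it through.** **Reading the passages together**

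1. The request covers co-interventions in general. Oral analgesics are introduced by the word including, so they are an example and not the limit.
2. Section 2.15 supplies the definition and expressly brings in the topical NSAIDs and footwear changes that the package recommends. Topical NSAIDs would fall under its creams and medication examples in any case.
3. The package goes to both arms. So for either arm, taking up the advised item means using a co-intervention, which means not doing what was requested. No other section breaks this chain.

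**The plan's own figures**

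The protocol gives no co-intervention rates and no calculation for this outcome, so there is nothing to reproduce on the point itself. Its one computed figure, the sample size in section 2.19, is unaffected: a difference of 1.1, SD 2.2, two-sided alpha 0.05 and 80% power give 63 per arm by the normal approximation, and 126 / (1 − 0.10) = 140, as stated.

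**How large the dilution could be (illustration)**

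All of these inputs are assumptions:

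- a = use of other treatment in the sham arm, 0.30
- b = use of other treatment in the orthoses arm, 0.15
- g = use of advised items, equal in both arms and independent of other-treatment use, at 0.30, 0.50 or 0.70

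Proportion with any use:

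- sham: 1 − (1 − a)(1 − g)
- orthoses: 1 − (1 − b)(1 − g)

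The risk difference is therefore (1 − g)(a − b), so under these assumptions it shrinks in proportion to g.

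| g | Sham, any use | Orthoses, any use | Risk ratio (sham / orthoses) | Risk difference (points) | NNT | Power at 70 per arm |
|---|---|---|---|---|---|---|
| 0 | 0.300 | 0.150 | 2.00 | 15.0 | 6.7 | 57% |
| 0.30 | 1 − 0.70 × 0.70 = 0.510 | 1 − 0.85 × 0.70 = 0.405 | 1.26 | 10.5 | 9.5 | 24% |
| 0.50 | 1 − 0.70 × 0.50 = 0.650 | 1 − 0.85 × 0.50 = 0.575 | 1.13 | 7.5 | 13.3 | 15% |
| 0.70 | 1 − 0.70 × 0.30 = 0.790 | 1 − 0.85 × 0.30 = 0.745 | 1.06 | 4.5 | 22.2 | 9% |

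A larger assumed contrast behaves the same way. With 40% against 20%, the risk ratio of 2.0 falls to 0.58 / 0.44 = 1.32, 0.70 / 0.60 = 1.17 and 0.82 / 0.76 = 1.08, and power at 70 per arm falls from 74% to 38%, 24% and 14%.

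**How far this rests on equal uptake**

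Suppose instead that advised items are used by 50% of the sham arm and 30% of the orthoses arm, with other treatment again at 30% and 15%. Any use is then 1 − 0.70 × 0.50 = 0.650 against 1 − 0.85 × 0.70 = 0.405. The risk ratio is 1.60, still below 2.0, but the risk difference is 24.5 points, above 15. Pooling then adds to the absolute contrast. The direction of the effect on the absolute scale therefore depends on uptake that the protocol does not give, which is a reason to show the components and not only the total.

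**The case against.** The strongest reply has five parts.

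- **The request is mild.** Participants are asked only to attempt to avoid co-interventions, the one class named is oral analgesics, and some use is expected and documented. This stands as far as it goes. A reader might infer that participants face two commands they cannot both obey; the text supports an inconsistent message, not an impossible one. The inconsistency remains, because section 2.15 counts the advised items by name.
- **The pain outcome is not shown to be biased.** A reader might infer that the primary endpoint is contaminated. The documents do not support that. Both arms receive the same package and the same request, and participants are blinded by limited disclosure (section 2.8). Ambiguity common to both arms does not by itself distort the randomised pain contrast. This stands in full.
- **Section 2.20 does not define a single any-use composite.** It names frequency of co-interventions as an example, and tabulation by type could sit in an analysis plan that is not shown. This stands in part: the absence of a breakdown is not a fault in itself. But the definition that places advised items inside the outcome is stated in the protocol, and an analysis plan cannot repair instructions already given to participants.
- **The rates are assumed.** They are, including equal and independent uptake, and the last calculation above shows that this assumption matters. Even with no advised-item use, 30% against 15% has only 57% power, so the comparison is weak in any event.
- **Dropping the advised items would go too far.** Topical NSAIDs are a pain treatment, so a comparison confined to non-package treatments would omit something relevant to the very question it serves. This stands, and it shapes the fix.

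**Conclusion.** The contradiction is in the stated text: sections 2.3 and 2.10.3 discourage co-interventions, section 2.10.3 advises on two items, and section 2.15 counts those two items as co-interventions. The consequence is confined to the secondary outcome of co-intervention use, where dilution and poor interpretability are to be expected. In the illustration a risk ratio of 2.0 falls to between 1.26 and 1.06, on assumed rates of 30% and 15% and with equal, independent uptake of advised items at 30% to 70%. The actual size cannot be known from the protocol. The primary outcome, its ANCOVA and the sample size are not affected. The point is worth correcting because the correction costs little, not because the main result is at risk.

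**What to change.** **Wording.** Reconcile sections 2.3, 2.10.3 and 2.15 so that the request to participants and the definition of a co-intervention agree. Which clinical advice should prevail is for the investigators and is not judged here.

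**Analysis.** Before unblinding, prespecify between-arm comparisons, using the measures already named in section 2.20, of:

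- (a) items recommended by the package, with topical NSAIDs shown separately from footwear changes;
- (b) any other new treatment;
- (c) the total.

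Keeping all three leaves topical NSAIDs visible as a pain treatment while separating trial-advised care from the rest. The split is by type of treatment, since the items that section 2.15 lists for recording do not include the reason for use.

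**Cost.** No new data are needed, because section 2.15 already collects type, dates and dosage and asks about footwear. The analysis change adds a few table rows. The wording change has a real drawback if made during recruitment: earlier and later participants would have had different instructions. Section 3.1 gives a recruitment start in September 2023 and expects follow-up to finish by December 2024, so the wording change may come too late for many or all participants. The analysis split applies regardless, but loses its value as a prespecified comparison if it is left until after unblinding.
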